**Fig. 3 Fig3:**
[figure not shown]
Schematic representation for right hemicolectomy with D2 and D3 lymph node dissection. The green area indicates the mesentery that underwent removal

**Fig. 4 Fig4:**
[figure not shown]
Schematic depiction for extended right hemicolectomy with D2 and D3 lymph node dissection. The green area signifies the mesentery subjected to removal

**Fig. 5 Fig5:**
[figure not shown]
Intraoperative view for open D2 and D3 lymph node dissection

**Fig. 6 Fig6:**
[figure not shown]
Intraoperative view for laparoscopic D2 and D3 lymph node dissection

For hepatic flexure or proximal transverse colon cancer and suspicious infrapyloric and/or greater curvature lymph nodes, D3 lymph node dissection may include its removal.

#### Concomitant care

Routine concomitant care is consistent between the two groups. No specific or prohibited interventions or requirements have been identified for this trial.

#### Photographic recording and quality assessment of the removed specimen

Following the application of the clips and before crossing the vessels, a photo of the surgical field is captured to assess the compliance of the performed lymph dissection with the declared procedure.

Photographic recordings of the specimen are taken on both sides (intraperitoneal and retroperitoneal) to assess the preservation of the mesocolic fascia (Figs. 7 and 8).

**Fig. 7 Fig7:**
[figure not shown]
Photograph of the specimen after D2 and D3 lymph node dissection (intraperitoneal view)

**Fig. 8 Fig8:**
[figure not shown]
Photograph of the specimen after D2 and D3 lymph node dissection (extraperitoneal view)

The quality of the specimen is determined according to West classification [18], and this evaluation is conducted independently by a collaboration of the surgeons and pathologists.

#### Specimen preparation for pathologists

Lymph node extraction from the fresh specimen is performed by surgeons after photographic recording of the specimen on both sides (Fig. 9). All mesentery is meticulously separated into groups of lymph nodes. An exception is made for the area of the paracolic mesentery, which is limited by the size of the tumor. This exception is intended to determine tumor invasion into the mesentery, as well as extramural invasion, tumor deposits, tumor budding, and circular resection margin (CRM).

**Fig. 9 Fig9:**
[figure not shown]
Extraction of lymph nodes from the specimen

The mesentery of the colon is dissected, and all visible lymph nodes are well isolated. Separate containers with selected lymph nodes, distributed by each group, along with the mesentery from which they were extracted (for additional detection of lymph nodes and other findings), will be sent to the pathologist (Fig. 10).

**Fig. 10 Fig10:**
[figure not shown]
Final view for the pathologist after lymph node extraction

#### Specimen controlling process

The material was fixed for 12 h in 10% neutral formalin, after which the material was cut out by a pathologist according to the standard protocol. Selected fragments undergo standard dehydration process in the pathological departments from all centers. Several sections (2–4) with a thickness of 5–6 μm were formed from the paraffin blocks. Hematoxylin and eosin were used for staining. The prepared slides were examined by a pathologist under a microscope.

All macroscopic specimens collected will be stored in a 10% solution of neutral formaldehyde until the trial finished.

After finishing of the trial, sealed disposable containers with all collected specimens are used in agreement with the State Sanitary Inspection Regulation for medical institutions or in a centralized way (thermal neutralization—cremation).

#### Adjuvant chemotherapy

Adjuvant chemotherapy will not be administered for stage I of the disease or stage II without risk factors such as poor tumor differentiation, extramural invasion, intestinal obstruction, tumor perforation during surgery, less than 12 examined lymph nodes, or involvement of resection margins. In all other cases, a fluoropyrimidine and/or oxaliplatin regimen will be employed.

#### Follow-up

The entire follow-up process will be meticulously monitored by the investigators involved. Regular contact with patients will be established to implement the necessary follow-up strategies.Abdominal ultrasound every 3 months for the first 2 years, then every 6 months until the 5th yearCEA monitoring every 3 months for the initial 2 years, then every 6 months until the 5th yearChest and abdomen CT scans every 6 months during the first 2 years, then annually until the 5th yearColonoscopy every year for 5 years postoperatively

### Outcome parameters

#### Primary endpoint

A 15% increase in 5-year overall survival (OS) utilizing D3 lymph node dissection.

#### Secondary endpoint

5-year disease-free survival (DFS)Incidence of apical lymph node involvementIntraoperative complicationsPostoperative morbidityMortality

### Definition of endpoints

#### OS and DFS

OS is the proportion of individuals in a study (in each group) who are alive 5 years after receiving the intervention. OS is defined by any-cause mortality.

DFS is the proportion of individuals in a study (in each group) who are alive 5 years after receiving the intervention, without experiencing local or distant recurrence or death from any cause. For DFS, an event is defined as local or distant recurrence or death. Participants who are lost to follow-up during the 5-year period post-procedure will be classified as censored. The survival analysis will be conducted using Kaplan–Meier curves, with comparisons made using the log-rank test.

#### Incidence of apical lymph node involvement

The incidence of apical lymph node involvement is the histologically confirmed percentage of patients who underwent D3 lymph node dissection with positive lymph nodes.

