## Background and rationale

Colon cancer ranks 5th globally in both the number of newly diagnosed cases and the number of deaths among tumors in other locations [1]. The primary treatment method for patients with localized forms of colon cancer is surgery [2]. Lymphatic outflow from the right colon was described by Jamieson in 1909. In that study, regional lymph nodes were classified as paracolic, intermediate, and main nodes [3]. Nevertheless, the removal of all three levels of regional lymph nodes was not described in the literature as routine practice. Later, in Japan, questions regarding radical tumor removal began to emerge [4]. These questions primarily focused on the removal of the primary tumor and all regional lymph nodes, which were categorized into paracolic intermediate and apical nodes. Lymph node removal was classified as D1 (paracolic), D2 (paracolic and intermediate), and D3 (paracolic, intermediate, and apical). For stage II-III colon cancer, D3 lymph node dissection becoming mandatory [5].

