### Randomization and blinding

A simple 1:1 randomization was used in this study. A random number list was build using R studio software by an independent statistician and downloaded to electronic case report form (eCRF) with an allocation ratio 1:1 (D2 and D3 groups). After carefully selecting patients based on the inclusion and exclusion criteria, informed consent will be obtained by the corresponding investigators and the patients will be assigned to the corresponding intervention group. The trial is open-label, the surgeons are unblinded, and patients are clearly informed about the procedures they will undergo, as required by the healthcare systems of all centers in both countries. In the D2 lymph node dissection group, in case of intraoperative macroscopically suspicious apical lymph nodes are observed, the surgeon should remove them for ethical reasons. The patient will not be transferred to the D3 lymph node dissection group and will continue with follow-up as per the D2 group.

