### Sample size calculation

According to the SEER database (2004–2012) and AJCC 5th, 6th, and 7th editions, the 5-year overall survival for stage II right colon cancer was 68–84%, and for stage III, it was approximately 57 to 60% [21–23]. In the JCOG0404 trial, the 5-year overall survival for stage II-III was 91% [24]. Literature data suggests that the baseline survival for D2 lymph node dissection group is estimated to be 75% for stage II-III of the disease, and for D3 group, it is 90%, respectively. An anticipated difference of 15% in 5-year overall survival between D2 and D3 LND groups is expected. The log-rank test (Lacatos, proportion of surviving) was utilized in the PASS 11 program for sample size calculation. The power of the study is set at 80%, with a type I error 5%. An expected loss of follow-up is estimated at 15% for patients in each group. The enrollment period for patients is 3 years, and the total duration of the study will be 8 years. Based on aforementioned conditions, 239 patients should be included in the study (Table 1). Ultimately, 120 patients will be included in D3 group, and 119 patients in D2 group. The anticipated number of deaths in the D2 group is 24, and in the D3 group, it is 10.

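### The secondary endpoint on apical lymph node involvement is defined by positive nodes at any level, and its denominator can be read in two ways

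*Protocol article*

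**What the plan says.** In the protocol article, the section Secondary endpoint includes "Incidence of apical lymph node involvement". Under Definition of endpoints, the subsection of the same name gives the measure as the histologically confirmed "percentage of patients who underwent D3 lymph node dissection with positive lymph nodes". The word apical appears in the term being defined and not in the criterion.

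Other sections bear on how this is read:

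- Background and rationale sets out the node levels, with "D3 (paracolic, intermediate, and apical" as the three removed in a D3 dissection.
- Inclusion criteria admits patients with clinically node-positive (stage III) disease.
- Specimen preparation for pathologists states that "All mesentery is meticulously separated into groups of lymph nodes", and the text following Fig. 9 adds "Separate containers with selected lymph nodes, distributed by each group".
- Randomization and blinding provides for the D2 arm that "in case of intraoperative macroscopically suspicious apical lymph nodes are observed, the surgeon should remove them for ethical reasons"; such patients stay in the D2 group.
- Sample size calculation states that "120 patients will be included in D3 group".

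**The concern.** An endpoint definition should let two analysts with the same data arrive at the same percentage. This one does not. A D3 patient whose only positive node is paracolic or intermediate satisfies the written criterion, although that patient has no apical involvement. An analyst who follows the sentence exactly would report nodal positivity at any level under the name of apical involvement.

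The denominator is also open. The final phrase can belong to the numerator (D3 patients who have positive nodes) or describe the group in which the percentage is taken (D3 patients with positive nodes, among whom apical involvement is counted).

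What is at stake is the meaning of one descriptive secondary result. It matters clinically because, on the article's own classification, the apical level is what D3 adds to D2. Trial status dates the end of recruitment (11 Sep. 2023) before protocol version 1.3 (12 Oct. 2023), and node pathology does not depend on the 5-year follow-up. The definition is therefore best fixed before this result is tabulated. The article does not say whether that has been done.

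**Working it through.** The plan gives no figure for this endpoint, so there is nothing to reproduce. The check sets the sections side by side and follows the wording through.

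**Step 1: which patients meet the criterion.** The criterion requires D3 dissection and histologically positive lymph nodes. By Background and rationale, a D3 specimen contains three levels of node. By Inclusion criteria, node-positive patients are enrolled, so positive nodes below the apical level are to be expected. No other section limits the criterion to the apical level. Read literally, it therefore counts every node-positive D3 patient.

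**Step 2: the possible readings.** Let N be the number of patients who underwent D3, P the number of these with any positive node, and A the number with a positive apical node. Every apical-positive patient is node-positive, so A ≤ P ≤ N.

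| Reading | Formula |
|---|---|
| (a) Literal: any positive node, all D3 patients | P / N |
| (b) Apical-positive, all D3 patients | A / N |
| (c) Apical-positive, node-positive D3 patients | A / P |

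**Step 3: direction.**

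- (a) − (b) = (P − A) / N ≥ 0. The two agree only if every node-positive D3 patient also has a positive apical node.
- (c) / (b) = N / P ≥ 1. The two agree only if every D3 patient is node-positive, or if A = 0.
- Readings (a) and (c) cannot be ordered without knowing P and A.

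So (b) is never the largest of the three, and both alternatives can only equal or exceed it.

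**Step 4: size.** With the planned D3 group, N = 120. Each D3 patient whose positive nodes all lie below the apical level adds 1 / 120 = 0.83 percentage points to (a) and nothing to (b). The total excess is (P − A) × 0.83 percentage points. The article gives neither P nor A, so this goes no further.

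**Step 5: can the intended quantity be obtained?** Yes. Nodes are sorted and sent to pathology by group, so apical status should be identifiable separately from the other levels.

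**The case against.** The strongest reply is that context supplies the missing word. The heading and the subject of the sentence both concern apical nodes, so positive lymph nodes reads naturally as shorthand for those just named. Restricting the measure to D3 patients also fits an apical rate better than an overall node-positive rate, which would apply to both arms. Sorting the specimen by group points the same way. This largely stands: the apical meaning is the likely intent.

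It does not dispose of the point. Supplying the word apical removes reading (a) but does not strictly exclude (c). All D3 patients is the more natural denominator, yet the sentence does not fix it. The sections on intraoperative complications, postoperative morbidity and postoperative mortality each name the total number of patients as the denominator, so the article does settle endpoints at this level of detail. This is therefore a stated rule worded wrongly, and not detail left to an analysis plan that is not shown.

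A second reply is that confidence intervals, a further rate among node-positive patients and a listing of D2 patients are matters for an analysis plan. That is accepted: their absence is not part of this point.

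**Conclusion.** The definition is defective as worded. Taken literally it yields the node-positive rate among D3 patients, which is equal to or higher than the apical rate, and it leaves the denominator open. The conclusion on direction rests only on apical nodes being among the nodes a D3 dissection removes; it needs no outside rate.

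Three stronger inferences are not supported.

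- A reader might infer that the trial will report the wrong quantity. The heading and the handling of the specimen make the apical reading likely, so this is a risk created by the wording and not a demonstrated outcome.
- A reader might infer that the apical rate would be overstated several-fold. The article gives no node-positive or apical-positive rate, so no multiple can be derived from it.
- A reader might infer damage to the main result. The primary endpoint is overall survival; neither it nor the sample size uses this definition.

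This is a wording error in one secondary endpoint. It is worth correcting because the correction is simple and the result would otherwise be open to different readings.

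**What to change.** Replace the defining sentence with one that fixes both parts of the fraction:

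- **Numerator:** among patients who underwent D3 dissection, the number with at least one histologically positive node in the separately submitted apical group.
- **Denominator:** all patients who underwent D3 dissection.

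Two additions are optional, and each should carry its own label so that it is not confused with the endpoint: the same numerator over node-positive D3 patients, and a listing of D2 patients whose suspicious apical nodes were removed, with the histological result. The listing would be a matter of reporting only and would change nothing in how those patients are managed or analysed.

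The cost is one sentence in the protocol or analysis plan. Since nodes already go to pathology by group, no new data should be needed.

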#### Intraoperative complications

All intraoperative complications will be diagnosed during the operation.Vascular injury: An unintentional full-thickness defect of the vessel (arteries and veins) wall caused by surgical manipulations. Arterial vessels include the ileocolic, right colic, middle colic, accessory middle colic, gastroepiploic, superior mesenteric, and aorta. Venous vessels include the ileocolic, right colic, gastrocolic trunk and its tributaries, middle colic, superior mesenteric, and cava.Tumor rupture/perforation: An unintentional partial or full-thickness defect of the colon wall where the tumor is located, caused by surgical manipulations.Abscess perforation: An unintentional defect in the abscess capsule accompanied by the release of pus into the abdominal cavity.

The method of aggregation for all intraoperative complications will involve calculating the proportion of patients who experience complications during the operation relative to the total number of patients. Group comparisons will be conducted using the chi-square or Fisher’s exact test.

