#### The boundaries of D2 and D3 lymph node dissection

The proximal boundary of D2 lymph node dissection is defined by the location of mesocolon fixation to the Gerota’s fascia and the descending duodenum. In D3 lymph node dissection, the additional boundary extends to the head of the pancreas, up to the gastroepiploic vein and the lower edge of the pancreatic neck.

The distal boundary for D2 lymph node dissection starts from the ileum, 10 cm from the cecum, continuing 1 cm below the projection of ileocolic vessels until 1 cm laterally from the superior mesenteric vein (SMV). For D3 lymph node dissection, the distal resection margin additionally includes the opening of the anterior surface of the SMV, 1 cm below the origin of ileocolic vein. Paracolic lymph nodes should be removed at a minimum distance of 10 cm from the tumor in both the proximal and distal direction.

The lateral border for D2 and D3 lymph node dissection is defined by the white line of Toldt.

The surgical trunk (medial boundary) for D2 lymph node dissection is set at 1 cm from the lateral edge of the SMV at the level of the ileocolic artery and vein, extending proximally to the anterior surface of the duodenum. The head of the pancreas and origin of the feeding arteries are not visualized, along with the superior mesenteric vein and Henle’s trunk.

The surgical trunk (medial boundary) for D3 lymph node dissection is the medial side of the SMV from the lower border of the pancreatic neck to 1 cm below the origin of the ileocolic vein (Figs. 3, 4, 5, and 6). The anterior surface of the SMV, origin of the feeding vessels, and ligation of the intestinal tributary of Henle’s trunk serve as anatomical landmarks of complete D3 lymph node dissection. When the ileocolic artery and/or right colic artery pass behind the SMV, the ligation of these arteries is carried out at the lateral side of the SMV.

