#### Postoperative morbidity

All postoperative morbidity will be diagnosed within 30 days after the procedure, except for postoperative diarrhea.Postoperative lymphatic leakage: Includes lymphatic fistula, lymphorrhea, lymphocele, lymphatic ascites, and special forms (chylous leakage), classified according to the Lv classification [19].Anastomotic leakage: A defect of the intestinal wall at the anastomotic site leading to a communication between intra- and extraluminal compartments. The severity is graded based on clinical management impact. Grade A anastomotic leakage results in no change in patients’ management, whereas grade B leakage requires active therapeutic intervention but is manageable without re-laparotomy. Grade C anastomotic leakage requires re-laparotomy [20].Postoperative diarrhea is loose stool, watery stool, or mucous stool three times or more a day within 6 months after the operation.

The aggregation method for all postoperative morbidities will involve calculating the proportion of patients who experience complications within the first 30 days post-operation relative to the total number of patients. Group comparisons will be conducted using the chi-square or Fisher’s exact test.

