### Reporting of postoperative complication

All potential harms will be collected systematically. MedDRA will be used to classify any potential harms, and all harms will be reported according to the Clavien-Dindo classification [26].

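### The two tested complication proportions are defined through three items each and are not tied to the harms the trial records, so the arm comparison may understate a D3 excess

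*Protocol article*

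**What the plan says.** Under Definition of endpoints, the Intraoperative complications section gives three items:

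- "Vascular injury: An unintentional full-thickness defect of the vessel (arteries and veins) wall caused by surgical manipulations". The vessels are then named and include central ones: "Venous vessels include the ileocolic, right colic, gastrocolic trunk and its tributaries, middle colic, superior mesenteric, and cava".
- "Tumor rupture/perforation: An unintentional partial or full-thickness defect of the colon wall where the tumor is located".
- "Abscess perforation: An unintentional defect in the abscess capsule accompanied by the release of pus into the abdominal cavity".

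The aggregation rule follows: "The method of aggregation for all intraoperative complications will involve calculating the proportion of patients who experience complications during the operation". Arms are compared by chi-square or Fisher's exact test.

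The Postoperative morbidity section also gives three items: lymphatic leakage (chylous leakage included), anastomotic leakage graded A to C, and diarrhoea up to six months. Its rule is "The aggregation method for all postoperative morbidities will involve calculating the proportion of patients who experience complications within the first 30 days post-operation", with the same tests.

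The section on the boundaries of D2 and D3 dissection describes what separates the arms: "In D3 lymph node dissection, the additional boundary extends to the head of the pancreas, up to the gastroepiploic vein", and on to the lower edge of the pancreatic neck. In D2 the pancreatic head, the superior mesenteric vein and Henle's trunk are left unexposed.

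Harms are also handled more widely. Reporting of postoperative complication says "All potential harms will be collected systematically", with MedDRA coding and Clavien-Dindo grading. Data monitoring has a designated physician enter every postoperative complication in the eCRF, and the monitoring committee reviews adverse events.

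**The concern.** The trial asks whether a more extensive dissection should be preferred, so its safety comparison ought to cover harms that the extension could plausibly cause. Both tested proportions rest on short lists with no category for other events, and neither refers to the harms data described later in the article. A site or analyst who takes the lists as the definition would count a patient with a duodenal or pancreatic injury, or with postoperative bleeding, as free of an endpoint event. An analyst who takes them as examples would count the same patient as having one. The first reading can hide a difference in the added field. The second leaves the endpoint undefined beyond three items, in an open-label, multicentre trial.

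**Working it through.** **Events against the text.** The article states no rate or target for either safety endpoint, so there is no figure to reproduce. The check is to follow each type of event through the sections.

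| Event | Meets a listed definition? | Covered by the general harms text? | Between-arm comparison specified? |
|---|---|---|---|
| Injury to superior mesenteric vein or artery, or gastrocolic trunk | Yes | Not needed | Yes |
| Pancreatic or duodenal injury at operation | No | Unclear: that section is headed as postoperative | No |
| Bowel injury away from the tumour | No: the perforation item is confined to the tumour site | Unclear, same reason | No |
| Lymphatic (including chylous) or anastomotic leakage | Yes | Yes | Yes |
| Diarrhoea | Yes, to six months | Yes | Yes, but the pooled proportion stops at 30 days |
| Postoperative bleeding, pancreatic complication, ileus, infection | No | Yes | No |
| Death within 30 days | Own section | Yes | Yes |

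The gap therefore has two parts. Non-vascular organ injury at operation has no defined event and no clear home in the harms text. The unlisted postoperative events are recorded and graded, but nothing links them or their grades to a tested proportion.

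**What a listed-only comparison omits.** In each arm let L be the proportion with at least one listed event, and U the proportion with an unlisted event and no listed one.

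- Full difference (D3 minus D2) = (L3 − L2) + (U3 − U2)
- Tested difference = L3 − L2
- Omitted part = U3 − U2

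If U3 exceeds U2, the tested difference understates the D3 excess by exactly that amount. If U is equal in the two arms, the difference in proportions is unaffected. The article gives neither U3 nor U2.

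**Scale.** Sample size calculation gives 120 patients in D3 and 119 in D2 (239 in total). One D3 patient is 1/120 = 0.83 percentage points. Purely as an assumption, U3 − U2 of 3% to 8% would be 0.03 × 120 = 3.6 to 0.08 × 120 = 9.6 patients. No source in the article supports that range; it only shows what such a difference would mean in patients.

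**Sensitivity of the tests.** Power is about Φ((|Δ| − 1.96·SE0)/SE1), where SE0 is the pooled and SE1 the unpooled standard error, two-sided 5%, with 119 and 120 patients. The rates are again assumed:

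- 2% against 5%: 24%
- 5% against 10%: 31%
- 10% against 20%: 58%
- 5% against 15%: 73%

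A non-significant result would be weak evidence of equal safety even with a complete endpoint. Leaving out part of a true excess would weaken it further.

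**The case against.** The strongest reply is that nothing closes the lists. Both sections open with, and aggregate over, all complications or morbidities, and neither says that only the named items count. Where the article wants a restriction it says so, as it does for emergency cases in the exclusion criteria. The named items could simply be those needing an operational definition. This stands: a closed list is something a reader might infer from the form of the definitions, not something the text states. It does not rescue the endpoint, because the text never says that every recorded complication counts either.

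A reader might also infer that the harms of D3 go uncounted. The sections on monitoring and on reporting of postoperative complications contradict that for postoperative events. Nor do the lists miss most harms of the added field: central vessel injury, chylous leakage and diarrhoea are all named. Some missing items are not specific to D3, since D2 also reaches the duodenum and the colon mobilisation is described without distinction by arm. A bias towards D3 is therefore possible but not shown.

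Data analysis applies chi-square or Fisher's test to categorical variables generally, so other harms could be compared. That permits a comparison without specifying one.

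The complaint that a pooled proportion weighs mild diarrhoea like a grade C leak is weak on its own, because any at-least-one-event proportion does this. It is a reason to show components and a severity cut, not a separate fault.

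Finally, the article may condense a fuller list. But it does give the definitions, the aggregation and the tests, and the point concerns what those say. If the full protocol already counts every complication, a sentence saying so would settle most of it.

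**Conclusion.** The point holds in a limited form. The two tested safety proportions are defined through three items each and are not connected to the wider harms data. Read as definitions, they leave non-vascular intraoperative organ injury and postoperative bleeding, pancreatic complications, ileus and infection outside the stated arm comparison. D3 works on the pancreatic head and neck and D2 does not, so the comparison may understate a D3 excess. The gap is firmest for intraoperative organ injury, which the general harms text does not clearly cover.

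The direction assumes that unlisted events are more frequent with D3, which is plausible from the described field but not established by the article. The size cannot be derived. The survival endpoint and the 30-day mortality comparison are unaffected.

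**What to change.** - **Postoperative morbidity:** define the proportion as patients with at least one harm recorded under Reporting of postoperative complication, within the 30-day window already stated. Compare any grade and Clavien-Dindo grade III or higher between arms.
- **Components:** show lymphatic leakage, anastomotic leakage and diarrhoea separately. State the window for diarrhoea, because its six-month definition does not fit the 30-day proportion.
- **Intraoperative complications:** add unintended non-vascular organ injury to the three existing items.
- **Timing:** recruitment finished on 11 September 2023, so the operative and 30-day data already exist in an open-label trial. Record this as a dated change with its reason, made before between-arm safety results are examined.

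The cost is endpoint wording and a few more tables. Postoperative harms are already collected, but intraoperative organ injury may have to be drawn from existing operative records. The reported D3 complication rate may turn out less favourable.
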